##### Study variables

The variables are collected at different time-points during the study (Table 1). These include: sociodemographic variables (age, sex), anthropometric variables (height, weight, BMI, blood pressure), clinical variables (drugs and dosages), smoking habits (smoking, non-smoker, ex-smoker), presence of multiple disorders (Clinical Risk Group and identified in the computerized patient clinical history and the number of health problems as a proxy asset of multi-morbidity), presence of microvascular complications (diabetic retinopathy, diabetic nephropathy, and diabetic neuropathy), presence of macrovascular complications (ischaemic heart disease, stroke, peripheral vascular disease, and heart failure), laboratory variables according to the standard procedures of the laboratory of reference (HbA1c, blood count, renal function- creatinine, glomerular filtration rate, urinary excretion of albumin), liver function (Alanine Aminotrasferase (ALT), Aspartate Aminotransferase (AST), alkaline phosphatase, Gammaglutamil transferase (GGT)), lipid profile (total cholesterol, HDL-C, triglycerides, LDL-C, and non-HDL-C), and episodes of severe hypoglycaemia (episodes of hypoglycaemia that require the intervention of a third party for recovery will be recorded).

**Table 1 Tab1:** Study timeline, variables and procedures

	IG-1 and IG-2					Control group	
Data collected	Assessment (months)				Source	Assessment	Source
	0	3	6	12		Month 0 & Month 12	
Inclusion/Exclusion criteria	1 + 2	1 + 2	1	1 + 2	e-CRF	§	SIDIAP
Sociodemographic variables and comorbidities: *1. Age, height, gender, weight, BMI, duration of T2DM, medication (active component and dose),* etc.*...* *2. Pluripathology, clinical risk group*	1 + 2	1	1	1 + 2	eCAP	§	SIDIAP
Main variable: HbA1c	1 + 2	1	1	1 + 2	e-CRF eCAP	§	SIDIAP
Lipid profile and other laboratory variables: Total cholesterol, HDL, LDL, triglycerides, non-HDL, urea, creatinine, glomerular filtration rate, urine albumin, AST, ALT, FA, GGT. Systolic and diastolic blood pressure	1 + 2	1	1	1 + 2	eCAP e-CRF	§	SIDIAP
Smoking habit	1 + 2	1	1	1 + 2	eCAP e-CRF	§	SIDIAP
Sedentary lifestyle	1 + 2	1 + 2	1	1 + 2	e-CRF		
Detection of macrovascular complications *Ischaemic heart disease, stroke, peripheral artery disease, heart failure*	1 + 2	1	1	1 + 2	eCAP e-CRF	§	SIDIAP
Chronic microvascular complications detection *Diabetic retinopathy, diabetic nephropathy (albuminuria, renal failure), diabetic neuropathy*.	1 + 2	1	1	1 + 2	eCAP e-CRF	§	SIDIAP
Costs: *Cost of medication, laboratory tests, additional tests, cost of staff (visits), referrals, IT*	1 + 2			1 + 2	eCAP e-CRF	§	SIDIAP
*Costs:* *Urgent care, outpatient and hospital admissions*	1 + 2			1 + 2	e-CRF		
Satisfaction and quality of life of patients *DTSQ / ESDQoL*	1 + 2		1	1 + 2	e-CRF		
Professional Satisfaction *Specific Questionnaire*				1 + 2	e-CRF		
intensification/treatment adherence		1 + 2	1	1 + 2	e-CRF		
Occurrence of severe hypoglycaemia episodes	1 + 2	1	1	1 + 2	e-CRF		SIDIAP
“Patient Activation Measure” questionnaire (instrument for disease self-evaluation)	1 + 2	1 + 2		1 + 2	e-CRF		

*For the IG-1 (monographic + training of professionals + additional measures originated in phase 1), clinic visits will be carried out at baseline, 3, 6, and 12 months. For the IG-2 (training of professionals + additional measures originated in phase 1), clinic visits will be carried out at the time of inclusion (month 0), 3, and 12 months*

Variables related to healthcare costs are also collected and include the costs derived from the medication used (cost per patient per month of medication prescribed according to prices set by the Health Ministry), laboratory tests used (based on prices listed in the Catalan Health Institute service portfolio), supplementary tests, professional costs (the cost of patient visits), cost derived from the referrals to specialists, use of the emergency department, outpatient and hospital admissions, temporary disability, and consumption of testing strips for measuring blood glucose.

The INTEGRA study includes variables evaluated using specific questionnaires:Physical activity: this is assessed using the Spanish version of the Brief Physical Activity Assessment Tool questionnaire [24]. It contains two questions that are scored on a scale from 0 to 4. The sum of the scores of both questions are classified as follows: ≥ 4 total score = “sufficiently” active (encourage the patient to continue their activity) or 0 to 3 total score = “insufficiently” active (encourage the patient to increase their activity).Patient treatment satisfaction: this is assessed using the Diabetes Treatment Satisfaction Questionnaire (DTSQ) [25] in both the “status” and “change” versions validated for Spanish patients. It comprises 8 sections, each of which is rated on a scale from 0 to 6 points. The score of satisfaction with treatment is the sum of the 6 sections of the questionnaire, which can range from very satisfied (36 points) to very dissatisfied (0 points). The remaining 2 sections measure the perceived frequency of hyperglycaemia and hypoglycaemia from 0 (never perceived) to 6 (perceived most of the time), and they are scored separately.Quality of life: this is measured using the validated Spanish version of the Diabetes Quality of Life Questionnaire (ESDQoL) [26], which consists of 21 items, of which 19 relate to specific life domains. The items are scored on a 5-point scale of impact. The effects of diabetes on each of the domains are weighted according to their importance to the quality of life of patients, and the weighted average impact is obtained.Satisfaction of the health professionals before and after the interventions proposed in the study is assessed by a questionnaire divided into 4 sections; the first three assess aspects of organization, content, and structure, and the fourth refer to the overall assessment.Clinical inertia is evaluated through the questionnaire created by the RedGEDAPS [27]. This questionnaire consists of 5 questions with two possible answers (yes or no) that professionals should answer in each visit when HbA1c > 9%.Self-management of the disease is evaluated by the Spanish validated version of the Patient Activation Measure questionnaire [28]. This questionnaire evaluates patients’ ability to play an active role in their health care by assessing knowledge, skills, confidence, and behaviours. It consists of 13 questions in which there are 5 possible response options (strongly disagree, disagree, agree, strongly agree, N/P). The scores range in value from 38.6 to 53.0 (on a 0–100 theoretical point scale).

### Data collection

In the intervention groups (groups 1 and 2), sociodemographic, anthropometric, clinical, and laboratory variables are obtained from the clinical history and anamnesis of the subjects. The data obtained through the questionnaires are collected during the clinic visit according to the subjects’ responses. The variables related to health care costs are obtained from the SIDIAP database. In the control groups, all data will be obtained from the SIDIAP database.

For both groups, variables related to data are collected as described in Table 1 in the Electronic Case Report Form (e-CRF), specifically designed for the purpose of the study.

The consultation with the specialists is carried out in addition to any others that are deemed necessary, and the number and frequency of visits is derived from the interventions proposed to the patients (pharmacological and non-pharmacological).

### Evaluation of the effectiveness between the two intervention groups

The e-CRF has been used to perform an evaluation at baseline, 3, 6, and 12 months. Secondary aims, such as patient’s self-efficacy to implement changes in risk factors, the direct health costs of T2DM patients, and the impact on satisfaction and quality of life of patients, is assessed using the e-CRF data, and the other information will be obtained from SIDIAP database.

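### The IG-1 versus IG-2 evaluation is stated at 0, 3, 6 and 12 months, but Table 1 schedules HbA1c and severe hypoglycaemia in IG-2 only at 0 and 12; the two must be reconciled, and severe hypoglycaemia needs one common count

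*Protocol article*

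**What the plan says.** The section *Evaluation of the effectiveness between the two intervention groups* states: "The e-CRF has been used to perform an evaluation at baseline, 3, 6, and 12 months". It draws no distinction between groups or between variables. It adds that information not taken from the e-CRF will come from SIDIAP.

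Table 1, under *Study variables*, sets out months 0, 3, 6 and 12 and marks each cell 1, 2 or both. The HbA1c row reads "Main variable: HbA1c 1 + 2 1 1 1 + 2" and the severe hypoglycaemia row reads "Occurrence of severe hypoglycaemia episodes 1 + 2 1 1 1 + 2". In both rows IG-2 appears at months 0 and 12 only. The footnote says of IG-2 that "clinic visits will be carried out at the time of inclusion (month 0), 3, and 12 months", so IG-2 attends at month 3 but has no month-6 visit. Some items are collected in both groups at month 3; the Patient Activation Measure row, for example, begins "Patient Activation Measure” questionnaire (instrument for disease self-evaluation) 1 + 2 1 + 2".

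For severe hypoglycaemia, Table 1 names the e-CRF as the only source in the intervention groups and SIDIAP in the control group. The text defines the event by the need for third-party help but does not say what period each entry covers. *Data collection* says that clinical variables in the intervention groups come from the clinical history and from questioning the patient, and that collection follows Table 1.

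**The concern.** *Study design* makes IG-2 the control group for IG-1, so this is the comparison that tests the main intervention. A reader of the evaluation section would expect HbA1c to be compared between the two groups at months 3 and 6. The schedule provides no IG-2 values for that.

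Severe hypoglycaemia raises a second issue. The interventions aim to intensify glucose-lowering treatment, so a reader of the results will want to compare these episodes between groups. If one group is asked three times and the other once, a difference may partly reflect how often the question was put, or a real difference may be distorted. The control group adds a third pattern, routine records alone.

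**Working it through.** The plan gives no figure on this point, so the check is a reading of the schedule. The inputs are the evaluation section, the cells of Table 1, its footnote, and the definition of the main variable in *Statistical analysis plan*.

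**Step 1. Scheduled months by group, from Table 1.**

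| Item | IG-1 | IG-2 | Both groups |
|---|---|---|---|
| HbA1c | 0, 3, 6, 12 | 0, 12 | 0, 12 |
| Lipids, other laboratory values, blood pressure | 0, 3, 6, 12 | 0, 12 | 0, 12 |
| Severe hypoglycaemia | 0, 3, 6, 12 | 0, 12 | 0, 12 |
| Satisfaction and quality of life | 0, 6, 12 | 0, 12 | 0, 12 |
| Sedentary lifestyle | 0, 3, 6, 12 | 0, 3, 12 | 0, 3, 12 |
| Intensification/treatment adherence | 3, 6, 12 | 3, 12 | 3, 12 |
| Patient Activation Measure | 0, 3, 12 | 0, 3, 12 | 0, 3, 12 |

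**Step 2. Compare with the stated evaluation at 0, 3, 6 and 12 months.**

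- Month 6: nothing is scheduled in IG-2, in agreement with the footnote. No between-group contrast can be made from scheduled data.
- Month 3: physical activity, intensification/adherence and Patient Activation can be contrasted. HbA1c, laboratory values and severe hypoglycaemia cannot, although IG-2 attends.
- Month 12: every item in the table above is scheduled in both groups.

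Because *Data collection* refers to Table 1 for what is collected, the evaluation section cannot be carried out as worded.

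**Step 3. Primary variable.** This is HbA1c at the final visit minus baseline. It needs months 0 and 12 only, and both are scheduled in both groups.

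**Step 4. Recording of severe hypoglycaemia after baseline.** IG-1: months 3, 6 and 12, three entries. IG-2: month 12, one entry. Controls: SIDIAP.

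**Step 5. What unequal recording could do.** Assume equal true rates, and assume each entry captures only the previous *w* months. The document does not state *w*, so three values are shown. The apparent ratio is months covered in IG-1 divided by months covered in IG-2.

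| Assumed *w* | Covered in IG-1 | Covered in IG-2 | Ratio |
|---|---|---|---|
| 3 months | 0–3, 3–6, 9–12 = 9 | 9–12 = 3 | 9/3 = 3.0 |
| 6 months | 0–6, 6–12 = 12 | 6–12 = 6 | 12/6 = 2.0 |
| 12 months | 0–12 = 12 | 0–12 = 12 | 12/12 = 1.0 |

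Under these assumptions any distortion runs towards more episodes in IG-1. Its size depends entirely on a window that the document leaves open, and the range includes no distortion.

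**The case against.** The strongest reply is that the evaluation section only says when the e-CRF was used, not that every variable is contrasted at every time point. Table 1 and its footnote show the group-specific visits openly, and the main variable is already fixed as final visit minus baseline. On this view no HbA1c contrast at month 3 or 6 was planned, so none is lost. This stands in part: it removes any threat to the primary analysis. It does not remove the conflict, because the section is headed as the comparison of the two groups and names month 6, when IG-2 has no assessment at all.

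On severe hypoglycaemia, the reply is that it is not among the secondary aims, that no safety contrast is defined in the article, and that a full protocol or analysis plan may define one. Also, the month-12 entry may draw on the clinical history and so cover the whole year. All of this stands. It makes the problem a risk to any comparison that is made, not a demonstrated bias.

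Two stronger readings are tempting. A reader might infer that all interim comparisons of IG-1 and IG-2 are impossible. The documents do not support that: three items are collected in both groups at month 3, among them the Patient Activation Measure, which serves the self-efficacy aim that the evaluation section itself names. Routine records may also hold some unscheduled IG-2 HbA1c values, though incompletely. A reader might also infer that the hypoglycaemia comparison is biased. That would require knowing that the month-12 entry misses earlier episodes, and nothing in the article says so.

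A last objection concerns the remedy. A common electronic source does not equalise ascertainment if IG-1 patients are seen more often, because each contact is an opportunity for an entry. This is correct, and the fix states it as a limitation.

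**Conclusion.** The stated evaluation schedule conflicts with Table 1 and its footnote and must be reconciled. From scheduled data, HbA1c and severe hypoglycaemia can be contrasted between IG-1 and IG-2 only at months 0 and 12; physical activity and Patient Activation can be contrasted at 0, 3 and 12, and intensification/adherence at 3 and 12. The primary month-12 contrast is unaffected.

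Severe hypoglycaemia is recorded three times after baseline in IG-1, once in IG-2, and from a different source in controls. Any between-group comparison is therefore at risk of differential ascertainment. The size cannot be established from the document. The ratios of 1.0 to 3.0 rest on equal true rates and an assumed look-back window, and serve only to show that the effect could be nil or substantial.

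**What to change.** 1. Reword the evaluation section to agree with Table 1. Limit between-group contrasts to months at which both groups are assessed: 0 and 12 for HbA1c, laboratory values and severe hypoglycaemia, and the shared months, including month 3, for the items marked in both groups. Report IG-1 results at month 6, and IG-1 HbA1c at month 3, as within-group description.
2. Base any between-group comparison of severe hypoglycaemia on one count over the full 12 months, taken from the same electronic-record source and in the same way in all groups. Table 1 already names SIDIAP for this item in controls, and the *Discussion* says that SIDIAP contains all data entered into eCAP. Treat IG-1's month-3 and month-6 e-CRF reports as descriptive.
3. State what period the month-12 e-CRF entry covers.

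The cost is wording and a record extraction, with no extra visits. Adding the item at IG-2's month-3 visit is no longer an option on the article's own dates: recruitment ended on 31 October 2017, follow-up on 31 October 2018, and the article appeared in February 2019.

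Two limitations should be reported with the result. Routine records may miss episodes, and IG-1's more frequent contacts may still raise recording in that group. A common source removes the unequal e-CRF questioning, but only reduces the second effect.

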### Evaluation of the effectiveness in the three study groups

Data at baseline and at 12 months of the population of all three types of learning centres that meet the defined criteria for inclusion and exclusion will be compared. Criteria will be adequately defined using the ICD-10 codes, thoroughly specifying the temporary windows of the accepted values. Only the outcomes that include SIDIAP variables (as indicated in the Table 1) will be able to be evaluated; even those that are in the e-CRD will not be able to be assessed. This evaluation of effectiveness will be performed in two possible ways: i) following the patients who meet the inclusion criteria in 2015 until the end of the study in 2018 (cohort study), or ii) a cross-sectional study in 2015 and another in 2018.

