**Methods:**

This is a two-phase mixed method study, whose aims are the development of complex interventions and the assessment of their effectiveness. The main study outcome is a change in glycated haemoglobin (HbA1c) levels.

The INTEGRA study is divided into two phases. Phase 1: A qualitative study with a phenomenological approach using semi-structured interviews with the objective of determining the factors related to the participants and health care professionals that influence the development and implementation of a specific intervention strategy aimed at patients with poor glycaemic control of T2DM in primary care. Phase 2: Exploratory intervention study to be conducted in Primary Health Care Centres in Catalonia (Spain), including 3 specific health care areas.

The intervention study has two arms: Intervention Group 1 and 2. Each intervention group will recruit 216 participants (the same as in the control group) between the ages of 30 and 80 years with deficient glycaemic control (HbA1c > 9%). The control group will be established based on a randomized selection from the large SIDIAP (Sistema d’Informació per al desenvolupament de la Investigació en Atenció Primària) database of patients with comparable socio-demographic and clinical characteristics from the three provinces.

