##### Participants

The participants are T2DM patients with poor glycaemic control that meet all the inclusion criteria and sign the informed consent.

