### Sample size calculation

The sample size was calculated using the GRANMO v.7.12 (IMIM, Barcelona) programme. Considering an alpha risk of 0.05 and a beta risk of less than 0.2 in a bilateral contrast, it was necessary to include 72 patients in each group (intervention and control) to detect a difference equal to or greater than 1% of HbA1c [5] between the two groups. A common standard deviation of 1.46 [6] and a loss rate to follow up of 20% were assumed.

Considering that each physician/nurse that makes up the Basic Care Unit will coordinate their diabetic patients, a correction may be made due to a possible contamination in the analysis between individuals by assigning each Primary Care Team to intervention or control groups and taking into account the design effect. According to a study performed by our research group [16], we estimated that each GP would have 15 potential candidate patients with HbA1c > 9%. Assuming that the intra-class correlation coefficient for Primary Care is 0.05 [29], resulting in a 1.7 design effect, the required sample size will be 42 * 1.7 = 72 individuals in each group.

Each control or intervention group consists of 3 basic health areas, one in each geographical area, each with a mean of 10 BCUs and 15 individuals per basic care unit. Thus, the sample finally calculated to obtain statistical significance was 72 subjects per centre, leading to a total of 648 study subjects.

First patient enrolled in the study INTEGRA on 09/12/2015.

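### For the comparison with usual care, the intervention arms are the enrolled participants in most of the protocol but all criteria-meeting patients of the centres in the three-group evaluation section

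*Protocol article*

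**What the plan says.** Four places in the protocol article tie the intervention arms to enrolled people.

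- Abstract, Methods: "Each intervention group will recruit 216 participants (the same as in the control group) between the ages of 30 and 80 years".
- Phase 2, Participants: "The participants are T2DM patients with poor glycaemic control that meet all the inclusion criteria and sign the informed consent".
- Control group: controls are selected from SIDIAP to resemble the patients of the intervention groups. Their inclusion period runs from the first enrolment (9 December 2015) to the end of recruitment (31 October 2017), with 12 months of data per patient.
- Sample size calculation: 72 subjects per centre, 648 in total, to detect a 1% HbA1c difference.

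The section Evaluation of the effectiveness in the three study groups compares something else: "Data at baseline and at 12 months of the population of all three types of learning centres that meet the defined criteria for inclusion and" [...]. It identifies patients through ICD-10 codes and limits outcomes to SIDIAP variables, and it mentions neither consent nor enrolment. It then leaves two designs open. One is "following the patients who meet the inclusion criteria in 2015 until the end of the study in 2018 (cohort study"; the other is a pair of cross-sections in 2015 and 2018.

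The Statistical analysis plan section says that IG-1, IG-2 and control will be compared on the change in HbA1c from baseline to final visit. It does not name the population.

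**The concern.** The two populations answer different questions. Among enrolled participants, the contrast with usual care estimates what the intervention does for those who receive it, which is the stated aim and the basis of the 1% design difference. Among all criteria-meeting patients of the centres, it estimates what having the programme in the centre does. That average includes patients who never enrolled and so have neither the IG-1 monographic consultation nor the SMS messages. They can benefit only indirectly, through the training of their professionals.

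Followed literally, the three-group section would probably report a smaller effect than participants experience, and a reader would set it against a design difference meant for participants. With both populations written into the protocol, the choice between them could also be made after the results are known.

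**Working it through.** **1. Can the two descriptions be the same people?**

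| | Abstract, Participants, Control group, Sample size | Three-group evaluation |
|---|---|---|
| Entry | Criteria met and consent signed | Criteria met |
| Time of entry | 9 December 2015 to 31 October 2017 | Criteria met in 2015, or cross-sections in 2015 and 2018 |
| Follow-up | 12 months per patient | To the end of the study in 2018, or none within a person |

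A cohort fixed by eligibility in 2015 is not a group enrolled until October 2017, and repeated cross-sections follow no enrolled individual. The section's opening sentence (baseline and 12 months) also does not fit its own options. Loose wording for enrolled participants therefore does not explain the difference.

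**2. The plan's sample size reproduces.** Inputs from Sample size calculation: difference 1, SD 1.46, two-sided alpha 0.05, power 80%, loss 20%, ICC 0.05, 15 patients per GP.

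- n = 2 x [1.46 x (1.960 + 0.842)]^2 / 1^2 = 33.5; 33.5/0.8 = 41.8, so 42.
- Design effect = 1 + (15 - 1) x 0.05 = 1.7; 42 x 1.7 = 71.4, so 72.
- 72 x 3 centres = 216 per group; x 3 groups = 648.

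**3. Enrolled fraction.** The same section gives three areas per group, "each with a mean of 10 BCUs and 15 individuals per basic care unit". Candidates per group = 3 x 10 x 15 = 450. If 216 are recruited, f = 216/450 = 0.48. The 450 are potential candidates with HbA1c above 9%, before the other exclusions, so 0.48 is a floor. As an illustration only, if one third were excluded (my assumption), f = 216/300 = 0.72.

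**4. Effect in the centre-wide population.** With a 1.0-point effect in participants and a share s of it reaching non-enrolled patients, the effect is f + (1 - f) x s. The protocol gives no value for s, so the whole range is shown at f = 0.48.

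| s | 0 | 0.25 | 0.50 | 0.75 | 1 |
|---|---|---|---|---|---|
| Effect (HbA1c points) | 0.48 | 0.61 | 0.74 | 0.87 | 1.00 |

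**5. Power at the plan's design effect.** SE = 1.46 x sqrt(2 x 1.7/(0.8 x n)).

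- Enrolled, n = 216 per group, effect 1.0: SE 0.205, power 99.8%.
- All candidates, n = 450 per group, effect 0.48 (the lowest case): SE 0.142, power 92.3%.

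The second figure takes the centre-wide population on the control side too, as the three-group section is worded. With 450 against only 216 controls, SE = 1.46 x sqrt(1.7 x (1/360 + 1/172.8)) = 0.176, and power in the same lowest case is about 78%.

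**The case against.** The strongest reply is that the rest of the protocol already points to enrolled participants. The Control group section matches controls to the patients of the intervention groups. The Statistical analysis plan defines the main variable by a final visit, and Table 1 schedules clinic visits only for IG-1 and IG-2. This stands in part: the population is not wholly open, and most of the text leans one way. But it makes the three-group section the outlier; it does not remove it.

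Second, Study design makes IG-2 the control for IG-1 and calls the SIDIAP group an additional comparison. The IG-1 versus IG-2 evaluation has its own section, based on e-CRF assessments. This stands, and a reader who inferred that the main between-intervention contrast is compromised would be going beyond the documents.

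Third, a reader might infer that the estimated effect would be halved. The documents do not support that as an expectation. Halving needs zero spill-over and no further exclusions. Coaching training covers all professionals in the centres. In IG-2 nobody has the monographic consultation, so what non-enrolled patients there most clearly lack is the SMS programme. Recruitment beyond 216 would also raise the enrolled fraction; the Discussion speaks of recruiting as many candidates as possible.

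Fourth, a reader might infer a serious loss of power. At the plan's own design effect that does not follow when the section's population is used in every group. A larger design effect would lower power in either population, but that is a separate question.

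Finally, the centre-wide comparison has a merit: it avoids the volunteer selection that the Discussion lists as a limitation. That is a reason to keep it under its own label, not to leave two populations for one contrast.

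**Conclusion.** The contradiction holds, for the comparison of IG-1 and IG-2 with usual care only. The three-group section specifies a population and time frame that cannot be the enrolled participants on whom the sample size and control selection rest. Following it would give a different and probably diluted estimate: 0.48 to 1.0 points for each 1.0-point effect in participants. That range assumes 216 enrolled out of 450 candidates per arm and spill-over anywhere from none to complete. Further exclusions, or recruitment above 216, would raise the lower end. The damage is to the size and meaning of the estimate and to the pre-specification of the analysis; the documents support neither a halved effect as the likely result nor a claim that the trial becomes underpowered. It should be corrected, and the correction is small.

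**What to change.** In Evaluation of the effectiveness in the three study groups:

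1. State that the 12-month HbA1c contrast with usual care uses the enrolled IG-1 and IG-2 participants, indexed at enrolment, against the SIDIAP controls selected as the Control group section describes, with 12 months of follow-up from each control's index date.
2. Replace both options (the 2015 cohort and the 2015 and 2018 cross-sections) for this contrast. Changing the population phrase alone would leave the section contradicting itself.
3. State that participants' HbA1c comes from the e-CRF/eCAP, where Table 1 already places it. Study design describes SIDIAP as anonymised, so the source should be explicit.
4. Keep the comparison of all criteria-meeting patients as a separately labelled secondary analysis of the centre-level programme effect. Report the enrolled fraction beside it, and do not read it against the 1% design difference.

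The cost is a wording change here and in the analysis plan, plus one labelled analysis on records already held; no further patients or data collection are needed. The downside is that the enrolled contrast carries volunteer selection, which the secondary analysis helps to gauge.
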